### **Statistical analysis plan**

**Description of the participants' characteristics at inclusion** (sociodemographic characteristics). These variables will be described by their median, interquartile range, mean, standard deviation, or frequencies (%), as appropriate.

#### **Primary outcome**

The percentage, and its 95% confidence interval, of persons tested for HCV RDT AND HCV RNA and aware of their status among the total number of persons eligible residing in the region where the intervention takes place will be compared between the 2 arms.

An analysis stratified on age and province of location will also be performed.

#### **Secondary outcomes**

The percentage, and its 95% confidence interval, of persons tested for HCV RDT and aware of their status among the total number of persons eligible residing in the region where the intervention takes place will be compared between the 2 arms.

An analysis stratified on age and province of location will also be performed.

The number of persons with HCV active infection (positive HCV Ab and positive HCV RNA) and results given and explained among the total number of persons eligible residing in the region where the intervention takes place will be compared between the 2 arms

The number of persons with at least one consultation in the Provincial Hospital among the estimated total number of persons with active infection residing in the region where the intervention takes place will be compared between the 2 arms.

**Analysis of variance** (ANOVA) will be used to detect the significance differences between the primary and secondary outcome variables among the two clustered trial arms. Confidence levels, confidence intervals, and effect sizes will be computed. ANCOVA model will be conducted to analyse the main outcome intervention by taking baseline as a covariate, and other descriptive correlation statistics will be tested for the association between covariate.

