### 3. SCIENTIFIC RATIONALE

#### HCV situation in Cambodia

In Cambodia, a Southeast-Asian country of estimated 15,7 million (2016 – World Bank) inhabitants, the prevalence of HCV infection in general population ranges from 3 to 5% (1)(2)(3)(4). A recent cross-sectional survey conducted by the University of Health Sciences (UHS) in four diverse geographical areas including the capital city of Phnom Penh and three provinces (Battambang, Siem Reap and Preah Sihanouk) reports that among 425 people living with HIV (PLHIV), prevalence of positive HCV Ab was 6.8% and prevalence of positive HCV RNA was 5.4% (Pheng P, Poster MOPEA0090 at IAS2017, Paris). Since the 90s, Cambodian government implemented a large access to systematic screening of blood donation for HBV and HCV and generalization of single use syringes. This latter action is particularly important because HCV transmission is mainly linked to parenteral infusions, surgery or endoscopy before years 2000 (5) and the most at risk population seems to be patients aged above 40 years (5)(6). In this population, prevalence of HCV infection increases with age and could reach 10 to 15% for persons aged more than 50 years old (MSF report). Systematic screening of HCV infection is not performed in Cambodia, and few patients with chronic HCV infections are aware of their status. Serological tests (ELISA and rapid tests) are available in public and private facilities while virological testing is limited to some laboratories in Phnom Penh. Predominant genotypes are genotypes 1 and 6 for more than 90% of patients (6)(7).

The treatment and care of HCV-infected patients are predominantly provided in the private sector and in 2 public hospitals (Kossamak hospital in Phnom Penh and Mong Reussey Referral hospital, Battambang province) within the MSF cohort. The use of Transient Elastography (Fibroscan) to assess liver fibrosis is rare as only two hospitals and one clinic in Phnom Penh are equipped. Patients with advanced stage of disease are referred to public hospitals. Hepato Cellular Carcinoma (HCC) is the first cause of cancer for men in Cambodia (8) and mainly linked to HBV and HCV infections(9)(10). Cirrhosis complications related to HCV seem also to be a major reason of hospitalization in public hospitals, but no precise data are available. Effectiveness of DAA within the MSF cohort was reported in 2 workshops: SVR12 was above 95% with the sofosbuvir/daclatasvir combination during 12 weeks.

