The national HIV/HCV coinfection guidelines launched in April 2017 and training was completed in 6 provinces: Banteay Meanchey, Battambang, Kampong Cham, Phnom Penh, Siem Reap, and Tbaung Khmum. To date, 11,393 patients have been screened which represent 42.1% of the ART cohort at 6 selected provinces, 560 are positive for HCV Ab (4.9%) and 372 patients have received confirmatory viral load tests result (262 positive, 70%). NCHADS plan to continue screening to reach 42000 patients screened at the end of 2018. Regarding these preliminary results (3.5% of positive HCV RNA), approximatively 1500 patients will be treated with DAA.

Ministry of Health has implemented a working group on the thematic of viral hepatitis B and C infections within the CDC (Communicable Disease Control) department. The National Strategic Plan (NSP) for Viral Hepatitis (VH) 2020-2024 has been developed during a series of multi-stakeholder consultations from 2017 to July 2019. This is the first NSP-VH 2020-2024 and is aligned with the National Health Services Strategic Plan 2016-2020. The goals are towards the elimination of viral hepatitis C as a public health threat by 2030, based on clear public health approach that promotes the rational, cost effective and safe use of medicines at the operational district level. Successively, the National Guidelines for management of viral hepatitis B and C

infections has been developed during a series of multi-stakeholder consultations from July to December 2019.

Operational researches are also needed to determine where the funds must be allocated the most efficiently. Interventions focused on the cascade of care seem the most appropriate measure and targeting general population aged more than 40 years old seems a priority in Cambodia as they cumulate higher level of prevalence and higher risk of advanced liver diseases.

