### Study overview

A facility-based testing intervention (group 1) will be compared to a community-based intervention (group 2). The study will be conducted in 2 separated provinces: Siem Reap and Kampong Cham provinces. Each province has approximatively one million of inhabitants and one

provincial hospital. Siem Reap province is composed of 4 ODs, 103 communes, 5 RHs and 88 HCs. Kampong Cham province is composed of 9 ODs, 107 communes, 9 RHs and 98 HCs.

For the study, one OD in Siem Reap province and 2 ODs in Kompong Cham province with approximately the same number of villages and inhabitants and the same distance from PHD will be selected. The districts are sub-divided into communes. Communes are further divided into villages. Villages are sub-divided into groups. A group is generally a combination of 50 households and one group will be defined as one cluster.

In order to decrease the risk of contamination between clusters, in each province, 4 geographic area, separated by communes not involved in the study, will be selected. A random selection of the geographic area in each province will be done to be part of arm 1 or 2.

**For each geographic area**, a multistage cluster sampling method will be used to select study participants:

1- A Probability proportional to size (PPS) sampling method to select 10 villages in each selected GA will be realized in a first step

2- Then, a preliminary mission will be organized in order to identify and confirm the location of HHs in the 10 selected villages. During this mission, information on age of inhabitants will be collected with the heads of village and a list of HHs will be identified

3- A Simple random sampling (SRS) method will be realized to select 100 households per village within the 10 selected villages

4- In each selected household, all persons aged more than 40 years old will be proposed to be part of the study.

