## **14. STATISTICAL ANALYSES**

### **Calculation of number of patients needed**

The study will be powered to detect an increase of HCV combined-testing uptake from 60% in the facility arm to 80% in the community arm among subjects older than 40 years.

According to Cambodia DHS report 2014, the average rural household size is 4 persons and the proportion of persons aged more than 40 years old is 25%, the cluster size is so estimated to 50.

The following assumptions and definitions will be used for the sample size calculation:

- an intra-class correlation of 0.01
- significance level  $\alpha = 0.05$
- power  $(1-\beta) = 80\%$
- clusters size: 50
- Design effect: 1.5

When accounting for the above-mentioned assumptions, 300 patients will need to be screened for HCV RNA and so, 6000 individuals aged above 40 years old will need to be screened by RDT (5% of patients are expected to have a positive HCV Ab). With an estimated median testing uptake of 60-70%, if we want to reach 6000 participants screened, it would be necessary to propose testing to 8000 participants from 160 clusters (80 clusters per intervention).

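### Active case detection gets only a crude comparison, while the age- and province-stratified analysis planned for both uptake endpoints would remove avoidable noise from it

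*Protocol*

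**What the plan says.** Under Primary outcome in section 14, combined-testing uptake is compared between arms, and then: "An analysis stratified on age and province of location will also be performed". The same sentence appears under Secondary outcomes, directly after antibody testing uptake. The next item, "The number of persons with HCV active infection (positive HCV Ab and positive HCV RNA) and results given and explained", is related to all eligible residents and compared between arms, with no stratification.

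The one covariate model does not fill the gap: "ANCOVA model will be conducted to analyse the main outcome intervention by taking baseline as a covariate". It concerns the main outcome, and age is not named.

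Two other places bear on this:

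- Section 3 (HCV situation in Cambodia) says that "prevalence of HCV infection increases with age and could reach 10 to 15% for persons aged more than 50 years old".
- Section 5 (Study overview) selects four geographic areas in each of two provinces and allocates areas to arms at random within province. It mentions no balancing on age. In the preliminary mission, "information on age of inhabitants will be collected with the heads of village".

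**The concern.** Antibody uptake is a proportion of eligible residents who act on an offer. Active case detection has the same denominator, but its numerator also requires infection. At equal uptake, an arm whose eligible residents happen to be older will find more infections. Of the two kinds of endpoint, this is the one with the more direct dependence on age, and it is the one without the age-stratified analysis.

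Only the age mix of the eligible residents is a nuisance. If one strategy reaches older people better, that is part of its effect and should stay in the estimate. Standardising to the age mix of all eligible residents removes the first and keeps the second, because the age-specific detection rates still differ between arms. What is at stake is the precision and readability of a secondary endpoint that is formally compared between arms.

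**Working it through.** The protocol gives no expected figure for the detection rate, so there is none to reproduce. Its planning prevalence is consistent with its own numbers: 6000 × 5% = 300 persons for RNA testing.

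**Inputs from the protocol**
- Uptake 60% v 80%, so a ratio of 0.80/0.60 = 1.33 if nothing else differs.
- Antibody prevalence in the over-40s: "5% of patients are expected to have a positive HCV Ab".
- RNA-positive share 262/372 = 70%, from an HIV cohort. It cancels in the ratio and only sets the case counts.
- 8000 persons, 4000 per arm. Each area has 10 villages × 100 households = 1000 households = 20 clusters of 50. With 80 clusters per arm, that is 4 areas per arm.

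**Assumptions, not in the protocol**
- 55% of eligible persons are above 50.
- The share above 50 varies between areas with an SD of 5 to 10 points.
- Flatter gradient: 3-4% antibody-positive at 41-50, overall held at 5%.
- Steeper gradient: 4% at 41-50 and 12.5% above 50 (midpoints of 3-5% and 10-15%).

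**Spurious ratio at equal uptake.** If the share above 50 differs by d, the ratio is 1 + d × g, where g = (prevalence above 50 − prevalence at 41-50) / overall prevalence.

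- Flatter, 3%: above 50 = (0.05 − 0.45 × 0.03)/0.55 = 6.6%, so g = 0.73.
- Flatter, 4%: above 50 = (0.05 − 0.45 × 0.04)/0.55 = 5.8%, so g = 0.36.
- Steeper: overall = 0.45 × 0.04 + 0.55 × 0.125 = 8.7%, so g = 0.085/0.08675 = 0.98. Because g is relative, it is the same if both prevalences are scaled down to 5% overall (2.3% and 7.2%).

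| d | 4% at 41-50 | 3% at 41-50 | steeper |
|---|---|---|---|
| 5 points | 1.02 | 1.04 | 1.05 |
| 10 points | 1.04 | 1.07 | 1.10 |

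To reach 1.33 by age alone, d must be 0.333/g: 34 points at the steeper gradient (55% to 89%). At 3% it is 46 points, which would take the share past 100%.

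**Variance.** For 4 v 4 areas the SD of d is SD_area × √(2/4), that is 3.5 or 7.1 points. The age component of the log-ratio variance is (g × that SD)². The sampling variance uses the expected cases at 5%: 4000 × 0.6 × 0.05 × 0.7 = 84 and 4000 × 0.8 × 0.05 × 0.7 = 112, so 1/84 + 1/112 = 0.0208.

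| gradient | g | age variance (SD 5 / 10) | share of total removed |
|---|---|---|---|
| 4% at 41-50 | 0.36 | 0.00017 / 0.00066 | 1% / 3% |
| 3.5% (middle) | 0.55 | 0.00037 / 0.00149 | 2% / 7% |
| 3% at 41-50 | 0.73 | 0.00066 / 0.00264 | 3% / 11% |
| steeper | 0.98 | 0.00120 / 0.00480 | 5% / 19% |

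Multiplying the sampling variance by the design effect of 1.5 (0.0313) lowers the steeper row to about 4% / 13%.

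**The case against.** The strongest objection is that stratifying a secondary endpoint is detail for a statistical analysis plan, and that a crude comparison is valid under randomisation. The second part stands: the imbalance is chance, and an interval that reflected the 8 allocated areas would already contain it. The first part has less force, because the protocol assigns the stratified analysis endpoint by endpoint and stops just before this one.

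Three stronger readings are tempting, and the documents do not support them.

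- **That an age difference would pass for a strategy effect.** Plausible differences move the ratio by 2-10%, against an expected 33%. If the interval is built on 50-household groups and misses area-level variation, that is a separate question about the unit of analysis.
- **That the precision gain is larger, about 9% and 28%.** Those figures follow if the 4%/12.5% prevalences are taken at face value, which means 8.7% antibody-positive and more cases. The sample-size section plans on 5%. The 3-5% is quoted for the general population, not for ages 41-50, and the 10-15% is only what prevalence could reach.
- **That the stratified result should be the main comparison.** In section 14 it is an additional analysis even for the primary outcome.

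It is also fair to say that section 5 describes a list of households with age information from heads of village. It does not say that age is recorded per person or linked to those tested. However, age-stratified uptake among all eligible residents already needs ages for untested persons, so detection requires no new kind of data.

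**Conclusion.** The point holds as a modest improvement in precision and interpretation. Section 14 leaves out of its stratified analyses the endpoint that carries an age-dependent prevalence as well as uptake, with only 8 areas to balance age. The spurious ratio is about 1.02-1.07 at the planned 5% prevalence, and 1.05-1.10 at the steeper gradient. The variance of the log ratio falls by roughly 2-7% at the middle of the flatter gradient, and by up to about 5-19% at the steeper one. In standard-error terms that is about 1-4% and 3-10%.

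All of these figures rest on the assumed 55% share above 50, the assumed between-area SD of 5 to 10 points and the assumed age gradients. That the omission exists, and that prevalence rises with age, rests on the protocol's text alone.

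**What to change.** Under Secondary outcomes in section 14, after the active case detection item, repeat the sentence already used for the two uptake endpoints: "An analysis stratified on age and province of location will also be performed". Add that the detection rates are standardised to the age mix of all eligible residents, and that the result is reported beside the crude comparison. The same age data and bands as in the stratified uptake analyses should serve; a cut at 50 would match the age the protocol itself singles out. Two bands by two provinces make four strata, with an average of (84 + 112)/4 = 49 expected cases each.

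The cost is one sentence and a little programming. The small downside is reliance on ages reported by heads of village for persons who were not tested.

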## 7. STUDY ENDPOINTS

### Primary endpoint

The primary endpoint is the **combined-testing uptake** defined as the number of persons tested for HCV RDT AND HCV RNA and aware of their status among the total number of persons eligible residing in the region where the intervention takes place

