increase the diversity of data, the focus groups will be conducted with a purposively selected sample of beneficiaries in the 8 geographical areas of the CAM\_C study.

While the exact number of participants cannot be precisely determined, based on the research question and the previous studies on similar topics, we expect to get approximately:

- 10 interviews with stakeholders (Head of health centres and head of ODs);
- 20 interviews with healthcare providers who are directly involved in the intervention such as HC staff, community health workers, and VHSG;
- 8 focus group discussions x 8 participants/focus group = 64 participants; 4 focus group discussions are to conduct among people who accepted to be tested for HCV and 4 focus group discussions are to conduct among people who did not accept to be tested for HCV.

We will conduct simple tabulations using Stata 17 (Stata Corporation, Texas, USA) to summarize the characteristic of participants (doctors, nurses, midwives, and other beneficiaries). The qualitative analysis will be done using grounded theory principles.

The study potentially provides policymakers with evidence that may be used to inform decisions regarding HCV testing/screening cascade in order to contribute to the debates surrounding HCV care and control.

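### Arms are randomised across 8 geographic areas, but Section 14 counts 160 household groups as clusters and names an ANOVA between arms with no area term

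*Protocol*

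**What the plan says.** **Allocation.** Under Study overview in Section 5, the protocol says that "in each province, 4 geographic area, separated by communes not involved in the study, will be selected", and then: "A random selection of the geographic area in each province will be done to be part of arm 1 or 2". Section 15.1 confirms the total by referring to a "sample of beneficiaries in the 8 geographical areas" of the trial. Within each area, 10 villages are sampled with probability proportional to size, and 100 households per village are drawn by simple random sampling. These draws select participants; they do not allocate arms.

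**Cluster.** The same section says: "A group is generally a combination of 50 households and one group will be defined as one cluster". The sample-size text in Section 14 follows that definition: ICC 0.01, cluster size 50, design effect 1.5, 160 clusters, 80 per intervention.

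**Analysis.** Section 14, under its Statistical analysis plan heading, states that ANOVA "will be used to detect the significance differences between the primary and secondary outcome variables among the two clustered trial arms" and that an "ANCOVA model will be conducted to analyse the main outcome intervention by taking baseline as a covariate". For the primary outcome it adds: "An analysis stratified on age and province of location will also be performed". The denominator of the primary endpoint in Section 7 is everyone eligible: "among the total number of persons eligible residing in the region where the intervention takes place".

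**The concern.** In a cluster-randomised comparison, the precision of the arm contrast is set by the variation between the units that were allocated. Here there are eight. Uptake may differ between areas for reasons unrelated to strategy, such as distance to a health centre or local leadership, and a chance imbalance of four areas against four goes straight into the difference between arms. An analysis that takes its error term from persons, or from 50-household groups inside the areas, does not fully count that variation. Its interval is too short, and a difference between areas can be declared a difference between strategies. Section 15.1 gives countrywide scale-up as the purpose to which the results will contribute, so the validity of the primary interval matters.

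The adjusted analysis does not repair this. It also has no area term, and its only named covariate, baseline, is not defined.

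**Working it through.** **Inputs from the protocol.** 8 areas; 160 groups; 8,000 persons offered testing; alpha 0.05 (sidedness not stated, two-sided taken); 60% versus 80%; power 80%; ICC 0.01 with cluster size 50.

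**Derived.**
- Groups per area: 160 / 8 = 20. This agrees with 10 villages × 100 households = 1,000 households = 20 groups of 50.
- Eligible persons per area: 8,000 / 8 = 1,000. This agrees with 1,000 households × 4 persons × 25% aged over 40.
- Areas per arm: 80 / 20 = 4.

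**The plan's own figures first.** Design effect = 1 + (50 − 1) × 0.01 = 1.49, which reproduces the stated 1.5. It is therefore the design effect for allocating groups of 50. The stated 300 persons for RNA testing does not follow as directly: 82 per arm (two-sided, no continuity correction) × 1.5 × 2 = 246. That gap is a separate matter.

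**Person-level ANOVA, all eligible (m = 1,000 per area).** If the analysis ignores area, the variance of the difference is understated by 1 + (m − 1) × ρ, where ρ is the area ICC. The actual type I error is 2 × [1 − Φ(1.96 / √(1 + 999ρ))].

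| Area ICC (assumed) | Design effect | Type I error |
|---|---|---|
| 0.0005 | 1.50 | 10.9% |
| 0.001 | 2.00 | 16.6% |
| 0.005 | 6.00 | 42.3% |
| 0.01 | 10.99 | 55.4% |

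**ANOVA on the 160 group means.** The total ICC is held at 0.01, and the share of it lying between areas is varied (simulation, no true effect, 70% uptake, 20,000 runs per scenario).

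| Share of ICC between areas | Type I error |
|---|---|
| 0% | 5.1% |
| 10% | 12.7% |
| 25% | 22.7% |
| 50% | 34.3% |
| 100% | 49.0% |

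**Only the roughly 300 RNA-tested persons (300 / 8 = 37.5 per area).** At area ICC 0.01 the design effect is 1 + 36.5 × 0.01 = 1.365, and the type I error is 9.3%. This is not the stated denominator, but the sample size is built on it.

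**Area-level analysis.** A t-test on 8 area means (6 df) gave 4.9% to 5.1% in every all-eligible scenario. With arm and province as factors (8 − 3 = 5 df, critical value 2.571) a simulation with two areas per arm in each province gave 5.0%.

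**Interval width.** At 60% versus 80% and area ICC 0.01, the half-width that ignores area is 1.96 × √(0.40 / 4,000) = 2.0 percentage points. At area level it is 2.571 × √(0.40 × 10.99 / 4,000) = 2.571 × 0.0332 = 8.5 points.

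**Power of the area-level model** (60% versus 80%, 1,000 per area, 5 df). The noncentrality is 0.20 / √(0.40 × [1 + 999ρ] / 4,000).

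| Area ICC (assumed) | Noncentrality | Power |
|---|---|---|
| 0.01 | 6.03 | 99.7% |
| 0.02 | 4.37 | 93% |
| 0.03 | 3.59 | 82% |
| 0.05 | 2.80 | 61% |

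With 37.5 per area and ICC 0.01, power is 75.5%, below the planned 80%.

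**The case against.** The strongest reply is that the text does not fix the unit of the ANOVA. It calls the arms clustered, and an ANOVA run on eight area percentages would be consistent with the sentence. A separate statistical analysis plan, not shown here, could say so. This stands in part. A reader might infer that the protocol commits to a person-level test with a false-positive rate several times 5%, but the text supports only that no area term is named.

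It is not a full defence. Section 14 does not leave the matter open: it names the test and counts 160 clusters with a design effect for groups of 50, against a different allocation unit in Section 5.

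Second, the ICC of 0.01 belongs to groups of 50. A reader might carry it to area level and quote 55% as the error rate. The protocol gives no area ICC, and placing all of the correlation between areas is the most inflating split. With none of it between areas, the group-level ANOVA keeps 5%. This objection stands, and it is why the results are given as ranges.

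Third, on baseline, a reader might infer that no such covariate can exist because uptake is zero before the intervention. The text never says that baseline means uptake. It may mean the sociodemographic characteristics described at inclusion or the socio-economic evaluation in the testing phase. What can be said is that the term is undefined, and that variables collected only from people who present for testing are not available for all eligible persons.

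Finally, a reader might argue that an exact permutation test could not go below 2/36 = 0.056. That needs a 2:2 split within each province, which the protocol does not state (an unrestricted 4:4 split gives 2/70 = 0.029), and no such test is planned. The point does not depend on it.

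**Conclusion.** The point holds as an inconsistency between the allocation unit in Section 5 and the cluster and analysis rules in Section 14, and it must be corrected before the primary comparison is made. That the area is the randomised unit and is absent from the named analysis is read directly from the document. The size of the error is conditional on two things the protocol does not give: the unit of the ANOVA and the area-level ICC.

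On the endpoint's own denominator, even an area ICC of 0.0005 doubles the person-level error to about 11%. At group level, one tenth of the stated ICC lying between areas is enough for about 13%. The error could also be close to nominal: about 5% at group level if no correlation lies between areas, and about 9% if only the RNA-tested persons were analysed at area ICC 0.01. These figures assume a two-sided test, equal-sized areas and four areas per arm.

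**What to change.** - State in Section 14 that the randomised geographic area is the unit of inference.
- Analyse the primary and the compared secondary outcomes in one of two ways: ANOVA on the eight area-level percentages with arm and province as factors (5 df if all eight areas contribute), or a mixed model with area as a random effect and small-sample degrees of freedom. Either serves. Take the risk difference and its 95% confidence interval from that model.
- Restate the design effect and power for eight randomised areas over a range of assumed area ICCs, and align Sections 5 and 14 on what a cluster is.
- Replace the undefined baseline covariate with variables known for all eligible persons, such as age (collected beforehand with the heads of village) and province.

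**Cost.** Changes to wording and analysis only, with no new data. Confidence intervals will be wider. With 1,000 per area, stated power stays above 80% up to an area ICC of about 0.03 and falls to about 61% at 0.05, which the sample-size text should acknowledge.
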